### Aim 2 Dependent Variables

Quiet breathing assessment: the pneumotachograph and pressure transducer connected to the face mask will record breath-by-breath flow, tidal volume, airway opening pressure, and breathing rate. After achieving a stable tidal volume, minute ventilation will be recorded for 5 minutes. The primary outcome for Aim 2 is an increase in tidal volume from baseline to postintervention 120-minute follow-up. Minute ventilation will be measured at baseline, just prior to study gas delivery, and 60 and 120 minutes post gas intervention.Respiratory muscle assessment: sEMGs of the respiratory muscles and the abductor pollicis muscle (nonrespiratory control muscle) will be recorded as described above to assess effects of intervention on motor control. To identify the muscles active during the quiet breathing assessment, the root mean square of each muscle signal will be averaged. Multimuscle activation will be calculated using a validated, vector-based measure that indexes the magnitude and pattern of composite electromyography activity [58]. The composite respiratory muscle activity from each participant with ALS will be contrasted to the averaged composite magnitude and pattern of the pooled control sample [59]. It is anticipated that composite magnitude will be lower in people with ALS than in controls and increase with intervention, especially with combined AIH + istradefylline.MIPs: inspiratory force generation will be assessed as the maximal voluntary pressure generated by the inspiratory muscles (MIP) against a closed valve, measured at the mouth [60]. Sniff nasal inspiratory pressure measures inspiratory force generation at the nose. These tests will be used as surrogate measures of respiratory strength. Each test will be repeated until 3 measurements are obtained within 10% variability; a minimum 20-second rest will be provided between measurements. A recent systematic review reported a high level of evidence for concurrent validity for MIP; however, interrater reliability was low [61]. To minimize interrater reliability, we standardized instructions given to participants across sessions and used the same rater for each participant. MIP will be measured at baseline, immediately prior to study gas delivery (4 hours after drug administration), and 60 minutes post gas delivery. Sniff nasal inspiratory pressure will be measured at baseline, immediately prior to study gas delivery, and 120 minutes post gas delivery. We hypothesize that these measures will be lower in people with ALS than with controls and will increase with intervention, especially with combined AIH + istradefylline.Maximal airflow testing: peak airflows will be collected with a pneumotachograph attached to the face mask during maximal inspiration (maximum inspiratory flow) and voluntary coughing (peak cough flow). Tests will be repeated for 3-5 trials; at least a 30-second rest will be provided between measurements, but participants may rest as long as needed. Maximum inspiratory flow will be tested at baseline, just prior to study gas delivery, and 60 minutes post intervention. Peak cough flow will be tested at baseline, just prior to study gas delivery, and 120 minutes post intervention. We hypothesize that these measures will be lower in people with ALS than with controls and will increase with intervention, especially with combined AIH + istradefylline.Maximal voluntary pinch force: maximal static voluntary pinch force will be included as a nonrespiratory control. Pinch has been recognized as a sensitive marker of ALS disease severity due to preferential thenar wasting [62]. A recent study found fair to good test-retest reliability for this measure [63]. Pinch force will be evaluated in a seated position with the arm at the side in 90-degree elbow flexion and neutral forearm and wrist. The test will be repeated until 3 measurements are obtained with <10% variability, with a minimum 30-second rest between measurements. Pinch force will be measured at baseline, just prior to study gas delivery, and 120 minutes post gas intervention. We hypothesize that these measures will be lower in people with ALS than with controls and will increase with intervention, especially with combined AIH + istradefylline.

Secondary outcome measures will be interpreted as exploratory in nature.

### Sample Size, Data Management, and Statistical Analysis

The sample size calculation was based on pilot data from 8 adults with ALS showing ventilation changes in AIH versus a sham condition. The preliminary data showed 10.3% (SD 23%) larger tidal volume and 10% (SD 29%) greater minute ventilation 60 minutes post AIH, as compared to sham. Published work in rodent spinal cord injury models indicates that istradefylline paired with AIH greatly enhances improvement in diaphragm activity versus AIH or drug alone (effect size of combined approach: *d*=1.92).

Additional preliminary data using caffeine as a nonspecific adenosine receptor antagonist conservatively suggested a capacity for a 10% additional gain in ventilation. With 16 crossover participants, a repeated measures ANOVA comparing 4 conditions across 4 time points, with a pooled SD of 15.3, will be sensitive to detect a difference of power of >0.8 (*f*=0.31; *F*_3, 36_=2.86; ρ=0.5; α=.05). A target sample of 24 participants will account for potential attrition. The design includes age-matched unaffected adults as a comparator group.

Descriptive statistics, including frequencies, means, SDs, and medians, will be used when appropriate. Continuous variables will be summarized with descriptive statistics, and categorical variables will be summarized with counts and percentages. Demographics and disease-progression variables will be reported descriptively; while these are not included in a priori analyses of study aims, they may be used in an exploratory manner to interpret findings as appropriate. Change scores and percent change scores will be calculated from baseline for follow-ups at postdrug or placebo administration, 60 and 120 minutes after gas intervention. We will attempt to minimize missing data by planning the study procedures and proper biosignal acquisition, thoroughly documenting the study administration and data collection, and collecting the essential information to complete the study aims. Should missing data points still occur, statistically valid analyses that appropriately address the missing values are maximum likelihood, expectation maximization, and multiple imputation [64]. Any statistical code or algorithms developed to analyze acquired data will be available and shared upon request.

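### The >0.8 power claim uses an SD of 15.3 that the reported pilot SD of 23% does not support; for combination versus AIH alone, a 10-point gain has power of about 0.37

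*Protocol article*

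**What the plan says.** All the power inputs stand in the protocol article under Sample Size, Data Management, and Statistical Analysis.

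- Basis: "The sample size calculation was based on pilot data from 8 adults with ALS".
- Pilot result, AIH against sham: "The preliminary data showed 10.3% (SD 23%) larger tidal volume and 10% (SD 29%) greater minute ventilation 60 minutes post AIH".
- Expected extra effect of adenosine antagonism, from caffeine data: these "conservatively suggested a capacity for a 10% additional gain in ventilation".
- Model: "With 16 crossover participants, a repeated measures ANOVA comparing 4 conditions across 4 time points", "with a pooled SD of 15.3".
- Claim: the design "will be sensitive to detect a difference of power of >0.8", with f=0.31, a critical F of 2.86 on 3 and 36 degrees of freedom, a correlation of 0.5 and alpha 0.05.
- A target of 24 is set to allow for attrition.

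Under Aim 2 Dependent Variables the endpoint is fixed: "The primary outcome for Aim 2 is an increase in tidal volume from baseline to postintervention 120-minute follow-up". Under Aims, Aim 2 is that the combination improves respiratory motor function compared with either intervention alone.

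**The concern.** The paragraph names the pilot as its basis and gives two SDs, 23% for tidal volume and 29% for minute ventilation. The calculation then uses 15.3. A pooling of 23 and 29 cannot give a value below both, and the article reports no other tidal-volume SD. Effect size f is the spread of the condition means divided by the SD, so an SD that is too small inflates f and the power.

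The pilot figures are also from 60 minutes and the add-on gain is for ventilation, while the primary outcome is tidal volume at 120 minutes. The text does not say that one is assumed to stand for the other.

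At stake is how the Aim 2 result will be read. A null result for the combination against AIH alone would carry a published claim of power above 0.8 that the trial's own pilot does not support for that comparison.

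**Working it through.** **Inputs (all from the sample-size section).** N=16, m=4 conditions, f=0.31, ρ=0.5, α=0.05, SD 15.3; pilot tidal-volume SD 23%; assumed additional gain 10%; pilot AIH effect 10.3%.

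**1. Reproduce the stated power.** For a within-participant factor, λ = f²·N·m/(1−ρ) = 0.31²×16×4/0.5 = 12.30. With 3 and 36 degrees of freedom the critical F is 2.87 and power is **0.805**. A single-group crossover of 16 would have 3 and 45 degrees of freedom and power 0.814, which makes no practical difference. The claim of >0.8 is correct for f=0.31.

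**2. Does 15.3 fit an SD of 23 at ρ=0.5?** The SD of a paired difference is SD×√(2(1−ρ)); at ρ=0.5 this equals the per-condition SD.
- If 23 is the SD of the AIH-minus-sham difference and 15.3 the per-condition SD, then ρ = 1 − 23²/(2×15.3²) = 1 − 529/468.2 = −0.13, not 0.5.
- If 23 is the per-condition SD, it differs from 15.3 directly.
- At ρ=0.5 both readings of 23 give a paired-difference SD of 23, so the power results below do not depend on which is meant.

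**3. Omnibus test at SD 23.** The spread of means implied by the plan is 0.31×15.3 = 4.74. Keeping it, f = 4.74/23 = 0.206 and λ = 0.206²×16×4/0.5 ≈ 5.44. Power is **0.43** (3, 36 df) or **0.44** (3, 45 df). With all 24 completing it is about 0.63 to 0.64.

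**4. Combination versus AIH alone.** Two-sided paired t test, noncentrality (difference/SD)×√n:

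| Difference | SD of difference | n | Power |
|---|---|---|---|
| 10 | 23 | 16 | **0.37** |
| 10.3 | 23 | 16 | 0.39 |
| 10 | 23 | 24 | 0.53 |
| 10 | 15.3 | 16 | 0.69 |
| 10 | 15.3 | 24 | 0.87 |

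At n=16 and SD 23, 80% power needs a difference of about **17 points** (17.2).

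**5. Combination versus sham.** If the two effects add, the difference is 10.3+10 = 20.3. At SD 23 and n=16, power is **0.91**.

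**6. Sensitivity to ρ, taking 23 as a per-condition SD (n=16).**

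| ρ | Omnibus power (3, 36 df) | 10-point contrast |
|---|---|---|
| 0.3 | 0.32 | 0.28 |
| 0.5 | 0.43 | 0.37 |
| 0.7 | 0.66 | 0.56 |
| 0.8 | 0.85 | 0.73 |

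**The case against.** **The arithmetic is sound.** This stands. The F test at f=0.31 has the stated power; the dispute is about one input.

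**The omnibus figure depends on means that the article does not give.** This also stands. With means of 0, 0, 10.3 and 20.3, omnibus power at SD 23 would be 0.92 to 0.93. That pattern gives f=0.55 at SD 15.3, so it is not what produced 0.31, and combination versus AIH alone remains a 10-point difference with power 0.37. A reader might infer from the SD gap that the whole trial has power of about 0.4, or can see only large effects in any comparison. The documents do not support that: the Objective in the abstract names sham as a comparator too, and that contrast could have power of about 0.91.

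**15.3 may be something else.** The article does not say what is pooled. If 15.3 were a within-participant residual SD, the paired-difference SD would be 15.3×√2 = 21.6, close to 23. That removes the conflict between the two SDs but does not rescue the power, because ρ=0.5 would then be counted twice. Without it λ = 0.31²×64 = 6.15 and omnibus power is 0.48. Also, an SD of 23 from 8 people has a 95% interval of about 15.2 to 46.8, so 15.3 is just inside it, at the favourable edge. A value taken from that edge needs a reason.

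**A condensed article may leave the derivation to the full protocol.** A missing derivation alone would carry little weight. Here the article publishes the claim, names its basis, and uses a number that does not match that basis.

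**The target is 24.** The 24 allows for attrition, and the claim is made for 16. The 10-point contrast passes 0.8 in the table only if the SD is 15.3 and all 24 complete.

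**The study is framed as preliminary.** It is, which limits the harm. The article nevertheless states a power for a hypothesis test.

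**Conclusion.** The point holds in a limited form. The stated power is correct for f=0.31, but the pilot SD on which the article says it relies does not support it. At SD 23 and ρ=0.5, power for a 10-point gain of the combination over AIH alone is about 0.37 at n=16 and 0.53 if all 24 complete; even at SD 15.3 it is 0.69 at n=16. Omnibus power is about 0.43 to 0.44, on the further assumption that the spread of means behind f=0.31 (4.74) is kept.

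These figures rest on the reported SD of 23%, which is itself imprecise, on the plan's ρ of 0.5, and on 60-minute values applying at 120 minutes. The effect of that last gap on power cannot be computed, because the article gives no 120-minute pilot figure; it should not be read as a further numeric loss.

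**What to change.** Revise the sample-size paragraph:

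1. Redo the power statement with the tidal-volume SD of 23%, or state what 15.3 is and where it comes from, and show power under both.
2. Give the four condition means behind f=0.31 and name the test or contrast to which the power refers.
3. For combination versus AIH alone, state power of about 37% for a 10-point difference and an 80%-power detectable difference of about 17 points, at n=16 and SD 23.
4. State as an assumption that the 60-minute pilot effect and SD carry over to the 120-minute primary outcome.

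The cost is a rewritten paragraph and a less favourable stated power. No participants are added and the conduct of the trial does not change. Whether Aim 2 is presented mainly as estimation is the investigators' choice and is not required by this point.

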### Aims

The objective of this study is to evaluate single and combined effects of selective A_2_A receptor antagonism and AIH on respiratory strength, resting breathing, and participant-reported symptoms in adults living with ALS and age-matched unaffected adults. The following two aims are proposed to test the hypotheses:

Aim 1: a single 20 mg istradefylline dose prior to AIH is safe and feasible. Dependent variables will include rate of adverse events (primary outcome), acute changes in vital signs (HR, respiratory rate, blood pressure [BP], etc), patient-reported symptoms (dyskinesias and dizziness), and study completion.

Aim 2: a single 20 mg istradefylline dose prior to AIH improves respiratory motor function when compared to either intervention alone. Dependent variables will include resting tidal volume (primary outcome), breathing rate and minute ventilation, respiratory muscle assessments via multichannel surface electromyography (sEMG), cough force, maximal inspiratory pressure (MIP), and maximal finger pinch force.

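### The only power statement, F(3,36), models four independent groups rather than the crossover, and power above 0.8 is not shown for Aim 2's contrasts

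*Protocol article*

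**What the plan says.** The protocol article, under Sample Size, Data Management, and Statistical Analysis, bases its calculation on "With 16 crossover participants, a repeated measures ANOVA comparing 4 conditions across 4 time points", "with a pooled SD of 15.3". It says that this "will be sensitive to detect a difference of power of >0.8", with parameters "f*=0.31; *F*_3, 36_=2.86; ρ=0.5; α=.05". It does not name the effect that the F test addresses (condition, time or their interaction), and it does not show how f was obtained. The expected benefit of adding an adenosine antagonist is introduced as preliminary caffeine data that "conservatively suggested a capacity for a 10% additional gain in ventilation".

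Under Study Visits, each participant has one session of each of the four conditions, in randomized order. Under Aims, the Aim 2 claim is that the drug given before AIH "improves respiratory motor function when compared to either intervention alone". Under Aim 2 Dependent Variables: "The primary outcome for Aim 2 is an increase in tidal volume from baseline to postintervention 120-minute follow-up".

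**The concern.** The printed degrees of freedom do not belong to the design described. Sixteen people who each cross over four conditions give 45 error df for a condition test, not 36. The value 36 arises when the 16 people are split into four separate groups. The text pairs four conditions with four time points, so the obvious mapping is conditions entered as groups and time as the repeated factor. The 3-df effect would then be time, averaged over all conditions including double placebo.

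A drift in tidal volume over a 7-8 hour visit, common to every condition, would make such a test significant without any treatment difference. This is the plan's only power statement. If the combination and AIH alone turn out not to differ, a reader could take that null result as coming from a trial with more than 80% power for that contrast, which the article does not show.

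**Working it through.** **Inputs.** From the sample size section: N=16, 4 conditions, 4 time points, f=0.31, ρ=0.5, α=0.05, pooled SD 15.3, 10% additional gain, and a pilot AIH-versus-sham tidal-volume SD of 23% (at 60 minutes). Assumptions: 15.3 is in % units (none are given), and the 10% gain, stated for ventilation, applies to the 120-minute change in tidal volume.

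**Reproducing the stated figure.** For a within-factor effect with k groups and m measures, λ = N·m·f²/(1−ρ), with df m−1 and (N−k)(m−1).

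- With N=16, k=4, m=4: λ = 16×4×0.31²/0.5 = 12.30; df 3 and (16−4)×3 = 36; critical F 2.866; power 0.805. This matches what is printed.

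**Alternatives that do not match.**

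| Set-up | df | Critical F | Power |
|---|---|---|---|
| One group of 13 | 3, 36 | 2.866 | 0.71 |
| Between-group condition effect, N=16, λ = 64×0.31²/(1+3×0.5) = 2.46 | 3, 12 | 3.49 | 0.18 |
| Group-by-time interaction, N=16, k=4, λ=12.30 | 9, 36 | 2.15 | 0.56 |

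One group of 13 gives the right df, but neither the stated N nor the stated power.

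**Omnibus condition test in the actual crossover.** With one group of 16 (k=1), the df are 3 and (16−1)(4−1) = 45. With λ=12.30 as before, critical F is 2.81 and power 0.814. If the same f applies to condition, the omnibus claim survives correction of the df.

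**Aim 2's contrasts.** Each contrast compares the 120-minute change under the combination with the change under one intervention alone, within person. The test is a two-sided paired t at 0.05 with n=16, 15 df and noncentrality √16 × (difference/SD of difference). For a 10-point difference:

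| SD of within-person difference | How it arises | Noncentrality | Power | Difference for 80% power |
|---|---|---|---|---|
| 15.3 | 15.3 is the SD of each change score, correlated 0.5 between conditions: 15.3×√(2×0.5) | 4×0.654 = 2.61 | 0.69 | 11.5 |
| 21.6 | change scores uncorrelated: 15.3×√2 | 4×0.462 = 1.85 | 0.41 | 16.2 |
| 23 | pilot AIH-versus-sham SD | 4×0.435 = 1.74 | 0.37 | 17.2 |

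The SD of 21.6 also results if 15.3 is the SD of a single measurement and ρ=0.5 holds between all 16 cells: √(4×0.5)×15.3 = 21.6.

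The power to succeed on both contrasts cannot exceed the power of the weaker one.

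**Condition-by-time interaction.** This has (4−1)(4−1) = 9 numerator df. If f=0.31 and λ=12.30 are carried over, power is 0.56 with 36 error df and 0.64 with 135. These two figures are illustrative only, because nothing shows that f was derived for this effect.

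**The case against.** A reader might infer that the printed calculation is certainly for a time main effect, and that the crossover therefore lacks the stated power. The article supports neither inference in full.

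- **The effect is not named.** Three numerator df fit four conditions as well as four time points. If the four groups were four treatment sequences and condition the repeated factor, F(3,36) and 0.805 would apply to condition. Against this, the Study Visits section describes only a random number table and no four-sequence scheme, and the four time points would then play no part in the calculation. Time remains the natural reading, not a proven one.
- **The omnibus test is not short of power.** With the same f and ρ, the within-participant condition test has power of about 0.81. There the defects are the df and the unnamed effect. This part of the objection stands.
- **The contrast figures need an SD that the article does not supply.** The article does not say whether 15.3 describes raw values, change scores or differences. That also stands, so the result has to be given as a range rather than as 0.69 alone.
- **Recruitment aims at 24.** If all 24 were analysed, one contrast would have power 0.87, 0.58 or 0.53 for the three SDs. But the claim is made for 16, and the 24 are there to absorb attrition.

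One might also leave the choice of contrast to a fuller protocol or SAP. But the point concerns figures that the article itself prints and that do not fit its own design.

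**Conclusion.** The concern holds in a limited form. The df and power printed for 16 participants belong to a model with four independent groups, not to a crossover in which each person receives all four conditions. The tested effect is unnamed; if it is time averaged over conditions, it does not address Aim 2.

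Power above 0.8 remains plausible for an omnibus condition test (about 0.81, if f=0.31 applies to condition). It is not shown for the combination against either intervention alone: 0.37 to 0.69 per contrast for a 10-point difference at n=16, and lower for both together. That range rests on difference SDs of 15.3 to 23 in % units and on carrying the 10% ventilation gain over to tidal volume. The printed arithmetic is internally correct; the fault lies in what it is applied to.

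**What to change.** Replace the F(3,36) sentence with one that:

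- names the tested effect and shows how f was derived for it;
- treats the conditions as within-participant (3 and 45 df for the omnibus test with 16 people);
- gives, at n=16, the power or detectable difference for both contrasts in 120-minute tidal-volume change: istradefylline + AIH versus placebo + AIH, and istradefylline + AIH versus istradefylline + sham AIH;
- states the assumed SD of the within-person difference, its source and units, and a range around it.

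No single figure from the table above should be written into the plan until the sponsor has established what the 15.3 represents. The sample size stays as it is. The cost is a rewritten sentence and a less favourable stated power.

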**Figure 3 figure3:**
[figure not shown]
Study design. The gray bars with arrows represent the timing of data collection procedures. AIH: acute intermittent hypoxia; IST: istradefylline.

Session order was determined by a random number table generated in advance of the enrollment of the first participant and maintained by the investigational pharmacist. Participants and investigators will remain blinded to istradefylline versus placebo for study administration and data analysis. Participants as well as the investigator collecting test outcomes will be blinded to AIH versus sham AIH. Prior to each study visit, the investigational pharmacist will inform the study coordinator which gas to administer during intervention (ie, hypoxic air for AIH vs normoxic air for sham AIH). Study team members conducting gas treatment cannot be fully blinded to AIH versus sham AIH due to monitoring of pulse oximetry oxygen saturation (SpO_2_), which is necessary for safety; thus, the investigator collecting testing outcomes will not be present during gas administration.

Participants will sit upright in a chair with the head and trunk supported while breathing through a sealed face mask. Resting ventilation, respiratory muscle activation, maximal respiratory pressures, maximal pinch force, and blood draws will be completed at the start of each study visit, then participants will receive study medication to be taken orally. After a 4-hour break, all outcome-measure testing will be repeated, followed by gas delivery. Postintervention testing will occur at 60 and 120 minutes following gas delivery. Table 2 delineates outcome measures taken at each time point.

Study visits are expected to last 7-8 hours, including equipment setup, repeated outcome measurements, oral administration of study medication, waiting periods, gas delivery, patient positioning and pressure relief, rest, and snacks or meal breaks.

**Table 2 table2:** Timing of variable measurements throughout study visit.

	Baseline	4 h post drug	Gas delivery	60 min post gas	120 min post gas
Adverse events	✓	✓	✓	✓	✓
Vital signs (HR^a^/BP^b^)	✓	✓	✓	✓	✓
Participant-reported symptoms	✓	✓		✓	✓
Borg dyspnea scale			✓		
Laboratory tests	✓	✓		✓	
Minute ventilation	✓	✓	✓	✓	✓
MIF^c^	✓	✓		✓	
PCF^d^	✓	✓			✓
MIP^e^	✓	✓		✓	
SNIP^f^	✓	✓			✓
Pinch force	✓	✓			✓

^a^HR: heart rate.

^b^BP: blood pressure.

^c^MIP: maximal inspiratory pressure.

^d^PCF: peak cough flow.

^e^MIP: maximal inspiratory pressure.

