## Results

This study received funding from the ALS Association starting in January 2022 and was registered on ClinicalTrials.gov in April 2022 (Multimedia Appendix 3). Recruitment for this study began in June 2022. As of January 2025, a total of 12 people with ALS and 8 age-matched controls have completed informed consent. Of these, 1 person with ALS was withdrawn after the screening visit, and 1 was withdrawn after 2 study visits. A total of 3 of the consented potential control participants were deemed ineligible following the screening visit. Thus, 10 participants with ALS and 5 age-matched controls have completed all study procedures. Recruiting is ongoing, and the final participant will complete the study by December 2025. The publication of results is expected by the end of 2026.

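### The primary tidal-volume comparison rests on change scores with no scale named; adjusting for the baseline already measured at each visit is more precise

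*Protocol article*

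**What the plan says.** All references are to the Protocol article.

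- **Aim 2 Dependent Variables** makes the primary outcome an increase in resting tidal volume from baseline to 120 minutes after the intervention. No scale is given.
- **Sample Size, Data Management, and Statistical Analysis** states that "Change scores and percent change scores will be calculated from baseline for follow-ups at postdrug or placebo administration" and at the later time points. It does not say which of the two scores is tested. The pilot input is a percentage, "10.3% (SD 23%) larger tidal volume".
- The only inferential model named is in the power statement of that section: "With 16 crossover participants, a repeated measures ANOVA comparing 4 conditions across 4 time points, with a pooled SD of 15.3". Neither a baseline covariate nor a visit-period term is mentioned.
- The same section lists maximum likelihood, expectation maximization and multiple imputation as valid ways to handle missing values.
- **Study Visits** has resting ventilation measured at the start of each visit, before study medication. It also says "Session order was determined by a random number table generated in advance of the enrollment of the first participant".
- **Results** reports 10 completers with ALS and one further ALS participant of whom it says "1 was withdrawn after 2 study visits".

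**The concern.** Subtracting the baseline gives it a coefficient of exactly 1. Tidal volume in a five-minute quiet-breathing record varies from one recording to the next, so the best coefficient is normally below 1, and the subtraction then adds baseline noise to the outcome. The ANOVA does not avoid this. If its four time points are the four at which quiet breathing is recorded, baseline is one level of the time factor, and its contrast of 120 minutes with baseline is the change score.

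Percent change divides by the same noisy baseline and tends to be skewed. Listing both scores without ranking them leaves two possible versions of the primary test. With 16 participants planned for analysis, avoidable variance matters, and so does a choice of scale left open.

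**Working it through.** **Inputs from the article:** 16 participants, 4 conditions, pooled SD 15.3, f = 0.31, a correlation of 0.5 among repeated measures, critical F(3, 36) = 2.86, two-sided level 0.05.

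**Assumed:** r, the within-participant correlation of baseline and 120-minute tidal volume at the same visit. The article does not give it. The 0.5 in the power statement is a correlation among repeated measures and cannot be taken over as r.

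**1. The stated power reproduces.** Noncentrality = 16 × 4 × 0.31² / 0.5 = 12.30.

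- With the stated 36 denominator df: critical F 2.866, power 0.805.
- With the one-group crossover df, 3 × (16 − 1) = 45: critical F 2.812, power 0.814.

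Both agree with the claim of more than 0.8.

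**2. Variance under each use of baseline.** Let the within-participant variance be σ² at both times.

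- Change score: 2σ²(1 − r)
- Baseline-adjusted: σ²(1 − r²)
- Ratio: (1 − r²) / [2(1 − r)] = (1 + r)/2

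A contrast of two conditions doubles both variances, so the ratio is unchanged.

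| r | change, 2(1 − r) | adjusted, 1 − r² | ratio | participants needed with change scores to match 16 adjusted (16/ratio) |
|---|---|---|---|---|
| 0.3 | 1.40 | 0.91 | 0.65 | 24.6 |
| 0.5 | 1.00 | 0.75 | 0.75 | 21.3 |
| 0.7 | 0.60 | 0.51 | 0.85 | 18.8 |
| 0.9 | 0.20 | 0.19 | 0.95 | 16.8 |

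If the variances differ (σ₀² at baseline, σ₁² at 120 minutes), the ratio changes but its direction does not. The variance saved is (σ₀² + σ₁² − 2rσ₀σ₁) − σ₁²(1 − r²) = (σ₀ − rσ₁)², which is never negative.

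**3. On the article's scale.** Reading 15.3 as a total SD with correlation 0.5 gives a within-participant variance of 15.3² × 0.5 = 117.0. At r = 0.5 the standard error of a contrast is:

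- change score: √(2 × 1.00 × 117.0 / 16) = 3.82
- adjusted: √(2 × 0.75 × 117.0 / 16) = 3.31

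A simulation of the 16-person crossover (1,500 runs, order random and unbalanced, no trend over visits) gave 3.79 and 3.24, a variance ratio of (3.24/3.79)² = 0.73. Power for a true difference of 10 rose from 0.716 to 0.837.

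**4. Overall F test.** If f = 0.31 describes the change score, the noncentrality is divided by the ratio. With 45 − 1 (baseline) − 3 (period) = 41 df, power is 0.811 at ratio 1, 0.832 at 0.95 and 0.915 at 0.75.

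**5. Visit period.** The table shows simulated standard errors with random unbalanced order and r = 0.5. The trend is an assumed change in the within-visit response, in points per visit.

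| trend | change, no period | change, with period | adjusted, no period | adjusted, with period |
|---|---|---|---|---|
| 0 | 3.79 | 3.98 | 3.24 | 3.39 |
| −3 | 4.17 | 4.05 | 3.69 | 3.51 |
| −6 | 4.69 | 3.99 | 4.34 | 3.48 |

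In every scenario run, with or without the period term, the mean estimate of a true difference of 10 lay between 9.8 and 10.3.

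**The case against.** The strongest reply is that the ANOVA appears only in the power statement, that the sentence on change scores stands among descriptive statistics, and that model terms are commonly left to an analysis plan or full protocol, neither of which is shown. That holds for the period term: its absence from the article is no error. It does not fully answer the baseline point, because the article itself defines the primary outcome as a change from baseline and itself lists two scores without choosing. It is also fair that r is unknown and that at r = 0.9 the gain is only 5%.

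Three stronger readings are tempting, and the documents support none of them.

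- **Incomplete participants would be discarded.** A classical repeated measures ANOVA does not itself use partial completers, but the article names maximum likelihood, expectation maximization and multiple imputation, and nowhere states deletion. The one partial completer so far adds 2 visits to the 40 from the 10 ALS completers, or 5%.
- **The planned contrasts are biased.** Condition order is randomized, so they are unbiased in expectation, as the simulation shows. If order was drawn without balancing, which the article does not say, the mean visit-position difference between two conditions would have SD √(3.33/16) = 0.46 visit. That is chance imbalance, part of sampling error.
- **Disease progression over the visits distorts the comparison.** A baseline taken at the same visit cancels slow decline in level. Only a trend in the within-visit response would matter, and the article gives no evidence of one.

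**Conclusion.** The point holds as a matter of precision and of naming one scale. With equal variances, baseline adjustment gives 0.65 to 0.95 of the change-score variance of a condition contrast for r from 0.3 to 0.9, and 0.75 at r = 0.5. The direction does not depend on r or on equal variances, apart from the single degree of freedom spent on the slope; the size does. The stated power is reproduced and is not in dispute. A period term is worth considering but not required: it pays if the response trends over visits and loses a little if it does not. This is a worthwhile improvement to the plan, not an error that invalidates it.

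**What to change.** Before unblinding, state one primary analysis of 120-minute tidal volume:

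- **Scale:** one, named in advance, either mL or log. The log keeps a relative interpretation without percent change. Report percent change descriptively only.
- **Model:** linear mixed model with condition, same-visit pre-dose tidal volume and the participant's mean pre-dose tidal volume as fixed effects, and participant as random effect. The participant mean makes the slope on the visit baseline a within-participant one.
- **Inference:** small-sample degrees of freedom, such as Kenward-Roger.
- **Participants:** fitted by likelihood, the model uses visits from partial completers, in line with the maximum likelihood option already listed.
- **Optional:** visit period (1 to 4), decided in advance.

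The cost is a few sentences, one degree of freedom for the within-visit baseline slope and three more if period is added, with a small loss of precision from period if there is no trend (3.24 to 3.39 in the adjusted model above). All the data are already being collected.
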